#### Mental health and quality of life

The Functional Assessment of Cancer Therapy-General rapid version (FACT-G7 [41]) is a 7-item measure for evaluating symptom/concern burden and quality of life (QOL) in advanced cancer patients over time. Despite beliefs that smoking cessation worsens mental health symptoms, previous studies indicate smoking cessation leads to no worsening and possibly improvement in mental health and quality of life; however, more research is required [42]. Research on QOL and smoking cessation amongst patients with cancer is very limited.

#### Provision of smoking cessation care

The outcomes described below will serve as a measure of staff adherence to the smoking cessation care model; Ask, Advise, Act/Help.
Advice to quit: as measured by any indication of a personalised description of the specific benefits of smoking abstinence during and after cancer treatment or endorsed use of evidence-based support (telephone counselling and pharmacotherapy), extracted by medical record audit and patient self-report. Advice to quit increases the likelihood that an individual will make a successful quit attempt [43, 44] and is an indicator of whether the implementation intervention has changed clinicians’ practice.Proactive referral to Quitline (including education around the benefits of Quitline): as assessed by review of Quitline records, medical record audit and patient self-report. Receipt of telephone cessation support (Quitline) increases the likelihood that an individual will make a successful quit attempt [45] and is an indicator of whether the implementation intervention has changed clinic practice.Prescription or provision of pharmacotherapy (including NRT and stop smoking medications) as assessed by medical record audit and patient self-report. NRT and stop smoking medications have a strong evidence base to assist smoking cessation [46–48] and provision of these is an indicator of whether the implementation intervention has changed clinic practice.

#### Cost effectiveness

Cost effectiveness will be measured by cost per successful quit attempt from a service-provider perspective. These data will be sourced from project and site records.

### Process measures

Advice to quit: as assessed by staff self-reported delivery of advice, patient self-report (including the source [doctor, nurse, radiation therapist, other], and content [whether cancer-related reasons for quitting were provided] and impact of the advice).Perceived competence with providing advice to quit: as measured by staff self-report.Referral to Quitline and quality of contacts: as assessed by staff and participant self-report.Provision or prescription of pharmacotherapy and attitudes: as assessed by patient and staff self-report.Attitudes and acceptability of providing/receiving cessation support: as measured by staff and patient self-report.System perspectives: including staffing, workload, leadership, technology, infrastructure, as assessed by interviews with key informants.Training in providing smoking cessation care: staff will be asked about if they have received smoking cessation care training and the form of training received.Experience and perceptions of Care to Quit intervention: as measured by staff self-report.

In addition to being important intermediate/process indicators, these data will be used to fully describe the implementation process as recommended for implementation studies [49] and measure differences in resource utilisation between the intervention and control groups.

### Covariates

Patient-reported sociodemographic characteristics (e.g. gender and age).Motivation to quit: the motivation to stop scale [50] has been adapted to assess motivation to quit amongst participants currently smoking at baseline and/or follow-up. The number of response options have been lessened from the original scale to: ‘I don’t want to stop smoking’, ‘I think I should stop smoking but don’t really want to’, ‘I want to stop smoking but I don’t know when I will’, ‘I really want to stop smoking and intend to in the next month’, ‘I really want to stop smoking and intend to in the next 6 months’ and ‘None of the above’. Participants who have stopped smoking at baseline or follow-up will be asked ‘How motivated are you to stay quit long-term and become permanently smoke-free?’ Response options range from ‘Not at all motivated’ to ‘Extremely motivated’.Quitting self-efficacy: participants currently smoking at baseline or follow-up will be asked the self-efficacy item from the International Tobacco Control four country survey [51] ‘If you decided to give up smoking completely in the next 6 months, how sure are you that you would succeed?’, which has been adapted from a 5- to 4-point scale of response options. Participants who have stopped smoking at baseline and/or follow-up will be asked ‘How confident are you that you will be able to stay quit long-term and become permanently smoke-free?’ Response options range from ‘Not at all confident’ to ‘Extremely confident’.Perceived benefits of quitting: participants will be asked at baseline and 7-month follow-up ‘How much do you think it would benefit your health if you were to quit smoking now or stay smoke-free?’ Response options range from ‘Not at all beneficial’ to ‘Extremely beneficial’.Smoking status of household members: at baseline and 7-month follow-up, participants will be asked ‘Besides yourself, do any other members of your household smoke cigarettes or use other tobacco products?’Perceived social support: at baseline, participants who are currently smoking/recent quitters will be asked ‘How much do you feel you could count on your family and friends to support you if you tried to quit smoking/stay smoke-free in the next 6 months?’ Response options include ‘Not at all’, ‘Somewhat’ and ‘A great deal’.Risk perceptions: at baseline and 7-month follow-up, participants will be asked to rate on a 5-point scale (ranging from ‘Strongly agree’ to ‘Strongly disagree’) how much they agree with the following statements: ‘Quitting smoking after a cancer diagnosis can make cancer treatments more effective’; ‘Quitting smoking after a cancer diagnosis increases the risk of side effects from cancer treatment’; and ‘Quitting smoking after a cancer diagnosis reduces the risk of secondary cancer or cancer recurrence’.Use of pharmacotherapy: at baseline and 7-month follow-up, participants will be asked ‘Have you used any of the following medications to help you quit/stay smoke-free?’ Response options will include ‘nicotine replacement products (e.g. gum, patches, lozenges, mouth spray, inhalator), Champix (i.e. Varenicline), Zyban (i.e. Bupropion)’.Financial distress: at baseline and 7-month follow-up, participants will complete the Financial Stress Scale [52, 53]. This scale asks participants ‘At any time since your most recent primary cancer diagnosis has any of the following happened to you because of a shortage of money?’ Response options include, for example: ‘Could not pay the mortgage or rent on time’. Based on prior research, this scale has been adapted to remove the ‘unable to heat/cool the home’ response option [54] and includes additional financial stressors related to a cancer diagnosis (e.g. ‘Could not pay for medical consultations or tests with GP or specialist’) [55]. Participants will also complete a financial distress thermometer, which asks ‘On a scale of 0 to 10, with 10 being extreme distress and 0 being no distress, please pick a number that describes how much financial distress you have been experiencing in the past week including today’.Mental health: as measured by the Patient Health Questionnaire-4 (PHQ-4 [56]) and an additional 2 items from the PHQ to assess panic attack history (‘In the last four weeks, have you had an anxiety attack—suddenly feeling fear or panic? Has this ever happened before?’). The PHQ-4 is a valid ultra-brief tool for detecting both anxiety and depressive disorders.Substance use: The Alcohol Use Disorders Identification Test—Brief (AUDIT-C [57]) is a 3-item screening tool used to identify hazardous alcohol use or active alcohol use disorders. In addition, participants are asked ‘Have you used cannabis for medicinal and/or recreational purposes? (over the last 6 months)’ with response options ‘Yes, No’, ‘How often did you use cannabis?’ with response options ‘Monthly or less, 2–4 times a month, 2–3 times a week, 4 or more times a week’ and ‘Do you mix tobacco with your cannabis?’ with response options ‘Yes, always or nearly always,’ ‘Yes, sometimes’ or ‘No, never or very rarely.’

#### Patient-completed measures

CATIs will occur within 2 weeks (baseline) and 7 months of recruitment.

#### Staff-completed measures

Online (or print if preferred by site) surveys will occur at the beginning of each study phase (baseline, intervention, post-intervention). These will be self-completed.

The assessment schedule is presented in Table 2.

### Sample size

The trial will recruit 2160 smokers (40 per site per 6 months over 3 years for each of nine sites). This sample size will provide approximately 80% power to detect a difference of 7% in smoking cessation (i.e. during the baseline phase 7% of those who were smokers or recent quitters at recruitment will achieve 6 months prolonged abstinence, while during the intervention phase 14% of those who are still smoking at diagnosis will achieve 6 months abstinence) at an alpha level of 0.05, assuming an intra-cluster correlation of 0.01 and a worst-case scenario of cluster autocorrelation equal to zero. This sample also provides over 90% power to detect each of the differences previously stated for the secondary outcomes.

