Staff will be invited to complete surveys online (or print if preferred by the site) at each study phase (baseline, intervention, post-intervention) to collect process measures data, experiences with and perceptions of the Care to Quit intervention and provision of smoking cessation care. Due to the stepped-wedge design of the trial, sites will enter intervention and follow-up periods at varying timepoints. Sites 1–3 will enter intervention at 6 months post baseline, sites 4–6 at 13 months post baseline and sites 7–9 at 19 months post baseline (Fig. 1). Staff surveys (Table 2) will therefore occur at varying timepoints from baseline across sites. The intervention period questionnaires will be completed mid-intervention period (i.e. 6 months post beginning of intervention period) for each cluster of sites (i.e. 13 months post baseline for sites 1–3, 19 months post baseline for sites 4–6 and 25 months post baseline for sites 7–9). The post-intervention period questionnaires will be completed at the beginning of the post-intervention period (19 months post baseline for sites 1–3, 25 months post baseline for sites 4–6 and 28 months post baseline for sites 7–9).

As the support provided at stages 1 and 2 will be delivered following assessment of site need (including current procedures, existing staff skills and experience) and tailored accordingly, further details of intervention dose (i.e. consultations, meetings, training materials provided) and mode of delivery (e.g., individual vs group, powerpoint presentations, videos) will be provided in the trial outcome paper. Project records will be used to document staff attendance at meetings and training. The delivery of smoking cessation support to patients will be implemented as part of routine care and tailored to site. Therefore, this may occur individually face to face at outpatient clinics, via telephone and/or telehealth and the amount or ‘dose’ of the support will differ.

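### Under a two-sided test with the ICC on the proportion scale, the stated 80% power fits four equal periods of 60 patients per site; on the protocol's own step calendar it is about 71%.

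*Protocol article*

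**What the plan says.** The Sample size section plans "2160 smokers (40 per site per 6 months over 3 years for each of nine sites". The control assumption is that "during the baseline phase 7% of those who were smokers or recent quitters at recruitment will achieve 6 months prolonged abstinence", and the intervention assumption is that "during the intervention phase 14% of those who are still smoking at diagnosis will achieve 6 months abstinence". The test is "at an alpha level of 0.05", with an ICC of 0.01 and "a worst-case scenario of cluster autocorrelation equal to zero". From these it concludes: "This sample size will provide approximately 80% power to detect a difference of 7% in smoking cessation". The section gives no period sizes, sidedness or ICC scale.

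The step times appear under Stage 2, where the staff surveys are scheduled: sites 1–3 enter the intervention at month 6, then "sites 4–6 at 13 months post baseline and sites 7–9 at 19 months post baseline".

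The Statistical methods section fits a logistic mixed model with a fixed effect for four phases (pre-intervention and three steps), a random effect for site and one for time within site. For 6-month abstinence it shifts the intervention indicator by 6 months. It does not say whether the phase boundaries shift as well.

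**The concern.** In a stepped-wedge trial, power depends on how patients are spread over periods as well as on the total. Once phase is a fixed effect and the autocorrelation is zero, a phase in which every site is in the same condition tells us nothing about the intervention. Steps at months 6, 13 and 19 in a 36-month accrual leave a short all-control phase, two mixed phases and a long all-intervention phase that holds nearly half the patients.

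If the 80% was derived for evenly spaced steps, it is not the power of the trial described. The protocol presents autocorrelation zero as the worst case, so readers will take 80% as a floor. A null primary result would then be read as evidence from a trial with a 20% chance of missing a 7-point effect, when that chance is nearer 29% under the conventional calculation.

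**Working it through.** **Inputs.** From Sample size: rates 0.07 and 0.14, ICC 0.01, autocorrelation 0, alpha 0.05, 40 patients per site per 6 months, and 9 sites × 6 half-years × 40 = 2160. From Randomisation: three sites per step. From Stage 2: steps at months 6, 13 and 19. From Statistical methods: four phases as fixed effects. Assumed here: two-sided test, ICC on the proportion scale, pooled variance, and every recruit supplying the 7-month outcome.

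**Formulae.** Pooled rate 0.105, so s² = 0.105 × 0.895 = 0.09398. With m patients per site in a phase, the variance of a site-phase mean is s² × (0.01 + 0.99/m). Each mixed phase compares three sites with six, so its contrast has variance (1/3 + 1/6) = 0.5 times that. Mixed phases combine by adding information. Power = Φ(0.07/SE − 1.96).

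**The plan's figure: four equal periods of 60 per site.** 9 × 4 × 60 = 2160.
- 0.01 + 0.99/60 = 0.0265.
- There are two mixed periods, so variance = s² × 0.5 × 0.0265 / 2 = s² × 0.006625.
- SE = 0.0250, z = 2.805, **power 80.1%**.

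This matches both the stated N and the stated power, but over 3 years it needs a step every 9 months.

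**The calendar at the stated accrual.**

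| Months | Patients per site | Conditions present |
|---|---|---|
| 0–6 | 40 | control only |
| 6–13 | 46.7 | 3 intervention, 6 control |
| 13–19 | 40 | 6 intervention, 3 control |
| 19–36 | 113.3 | intervention only |

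- Mixed phases: 9 × (46.7 + 40) = 780 patients. Single-condition phases: 9 × (40 + 113.3) = 1380.
- Information, in units of 1/s²: 2/(0.01 + 0.99/46.7) = 64.1 and 2/(0.01 + 0.99/40) = 57.6.
- Variance = s² / 121.6 = s² × 0.00822. SE = 0.0278, z = 2.518, **power 71.2%**.

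**Sensitivity under the same two-sided, proportion-scale settings.**
- Averaged or arm-specific variance: 71.7% or 71.9%.
- Autocorrelation 0.5: 71.7%; autocorrelation 1: 77.5%.
- Final phase ended at month 31: still 71.2%, because it adds nothing at autocorrelation 0.
- Phases and indicator both shifted by 6 months (12, 19, 25): 71.2%.
- Logit-scale calculation with the ICC still on the proportion scale: 71.0% to 73.9%.

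**Readings that reach about 80% on the calendar.**
- One-sided 0.05: 80.9%.
- Logit scale with a latent-scale ICC: log odds ratio 0.771, SE 0.275 (arm-specific variance) to 0.264 (pooled), power 80.1% to 83.2%.
- Indicator shifted by 6 months with phase effects left at months 6, 13 and 19: 84.1% (87.8% with arm-specific variance).

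**Detectable difference.** For 7% against 15%, s² = 0.11 × 0.89 = 0.0979, SE = √(0.0979 × 0.00822) = 0.0284, z = 2.82, power 80.5%. So about 8 points is detectable at 80%.

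**Loss to follow-up (illustrative; the protocol gives no rate).** Multiplying every phase size by 0.9, 0.8 or 0.7 gives about 68%, 64% or 60%.

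**The case against.** The strongest reply is that the paragraph leaves enough open for 80% to be right. Sidedness is not given, and the hypotheses are directional. The ICC scale is not given, and the planned model is logistic. The offset, read literally, moves only the indicator. Each of these yields 80% or more on the published calendar. The calendar itself sits in a paragraph about staff surveys and refers to Fig. 1, which is not available here.

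This stands against the stronger readings a reader might infer: that four equal periods are the only route to 80%, or that no choice of inputs rescues it. The documents support neither. That no autocorrelation value reaches 80% on the calendar is shown only for the two-sided, proportion-scale calculation without an offset applied to the indicator alone.

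It does not clear the paragraph. A one-sided test or a latent-scale ICC would have to be declared, and neither is. The indicator-only offset gains power partly from before-and-after contrasts inside a phase. For example, sites 7–9 would switch at month 25 within a phase running from month 19 to 36, and the phase effect does not adjust for time within it. The step months are stated plainly in the text, whatever the figure shows.

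Nor is the lack of a loss allowance an error in itself, since it may sit in a fuller document. The loss figures above are illustrations only.

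**Conclusion.** The point holds in conditional form. With a two-sided 0.05 test, ICC 0.01 on the proportion scale and autocorrelation 0, the stated power and sample size match four equal periods of 60 per site. On the protocol's own steps and accrual, power is about 71%, a shortfall of about 9 percentage points, and it stays below 80% even at autocorrelation 1. That the equal-period layout was the sponsor's method is an inference from the match; the protocol does not say so.

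It would be wrong to conclude that the trial's power is definitely 71%. That figure rests on the assumptions just listed, on complete follow-up, and on the offset either not entering or moving phases and indicator together. What is established is that the conventional calculation does not give the stated power for the described design, and that the protocol names none of the choices that would.

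**What to change.** Reconcile the Sample size, Stage 2 and Statistical methods sections by rewriting the sample-size paragraph for the actual phases: about 40, 47, 40 and 113 patients per site. State whether the test is one- or two-sided, the scale of the ICC, and whether the 6-month offset moves the phase boundaries as well as the indicator. Then recompute.

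If the conventional choices apply, report about 71% power at autocorrelation 0 and 77.5% at 1, with about 8 points (7% against 15%) detectable at 80%. Also give the figure after the loss to follow-up the sponsor expects. If another choice was made, state it, justify it and show its calculation.

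The cost is a rewritten paragraph and one recalculation. No extra patients and no change to accrual are needed. The price is a less favourable stated power if the conventional choices apply.

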### Randomisation

At each intervention ‘step’, 3 sites will be selected at random to commence the intervention. Centres will be randomly allocated to ‘step’, i.e. time of commencement of the intervention phase, by an independent statistician. For pragmatic reasons, three sites will be treated as their own cluster due to the concern for contamination if sites participated in the intervention at different times.

### Blinding

Participants, interviewers conducting the CATIs and data analysts will be blinded to the intervention phase. Because of the nature of the intervention, it is not possible to blind clinicians at participating sites or trial investigators to the sites’ allocation to ‘step’, i.e. time of commencement of the intervention phase once randomised. Participants will be blinded to treatment allocation.

### Data management

All data will be entered electronically via e-case report form using Research Electronic Data Capture (REDCap) tools [58] hosted at Hunter New England Local Health District NSW on a secure server. REDcap is a secure, web-based application designed to support data capture for research studies. The lead investigator (and/or delegate) and trial coordinator will conduct ongoing data checking and cleaning. Participant personal details will be accessed, used, and stored according to relevant legislations. Access to external health data (e.g. Quitline, health records) will only occur with the consent of the participant in accordance with protocols of relevant external agencies.

The current study is a trial of a non-invasive clinician-delivered smoking cessation support intervention. Clinicians will be trained in support strategies. These strategies will be delivered within the context of standard patient consultations. It does not involve administration of medicine or experimental therapeutic devices. In light of this an independent data safety monitoring board will not be convened.

### Evaluation

#### Statistical methods

Independent and blinded statisticians from the CReDITSS Unit at the Hunter Medical Research Institute, Australia, supervised by CI [name], will conduct analyses of the primary and secondary outcomes.

Logistic regression within a generalised linear mixed models framework will be used to model the primary and secondary outcome measures. All models will adjust for time using a fixed effect that describes the phase of the study (pre-intervention and each of the 3 steps). Variation between sites will be accounted for using a random effect for site and repeated measures on sites will be accounted for using a random effect for time within site. To estimate the intervention effect, a variable indicating when the intervention was active for a given site and time will be included in the models. As the timing of the 7 month CATI for some participants overlaps with intervention commencement, the analyses of 6 months abstinence will include a 6-month offset to the coding of the intervention indicator variable to allow the full effect of the intervention to be in place before estimating its effect.

There are no plans for interim analyses.

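### In the offset analysis of 6-month abstinence the intervention switch moves by 6 months but the phase effect does not, so part of any secular trend, mainly at sites 7–9, is credited to the intervention

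*Protocol article*

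**What the plan says.** All references are to the protocol article.

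- **Time term (Statistical methods).** "All models will adjust for time using a fixed effect that describes the phase of the study (pre-intervention and each of the 3 steps"). The model also has a random effect for site and one for time within site.
- **Meaning of a step (Randomisation; also Study design).** A step is the "time of commencement of the intervention phase, by an independent statistician".
- **Start dates (Stage 2 of the implementation section).** "Sites 1–3 will enter intervention at 6 months post baseline", "sites 4–6 at 13 months post baseline and sites 7–9 at 19 months post baseline".
- **Offset (Statistical methods).** "the analyses of 6 months abstinence will include a 6-month offset to the coding of the intervention indicator variable", and the purpose is "to allow the full effect of the intervention to be in place before estimating its effect". The sentence names the indicator only; nothing is said about moving the phase term.
- **Recruitment (Sample size).** "40 per site per 6 months over 3 years for each of nine sites", which makes 2160. The design is said to give about 80% power for 7% against 14%, with an intra-cluster correlation of 0.01 and cluster autocorrelation of zero.

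Six-month prolonged abstinence, to which the offset applies, is the primary outcome.

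**The concern.** In a stepped wedge, intervention time is on average later than control time. Calendar adjustment is what keeps a change in quitting over the years from being read as an intervention effect. It does this completely only if no site changes its coded condition within a level of the time factor. If a site does change inside a level, its control and intervention patients are compared with no adjustment for the time between them, and the model uses that comparison as evidence of effect.

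Here the coded condition changes on shifted dates while the time levels stay on the unshifted ones. At stake are some bias in the primary estimate, in the direction of whatever trend exists, and a standard error that looks smaller than an adjusted comparison supports.

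**Working it through.** **Step 1: dates.** The phases are cut at the starts: 0–6, 6–13, 13–19, and 19 to the end. If month 0 is the start of recruitment, three years puts the end at month 36. The coded switches are 6 + 6 = 12, 13 + 6 = 19 and 19 + 6 = 25.

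| Sites | Start | Coded switch | Phase containing the switch | Control / intervention months in that phase |
|---|---|---|---|---|
| 1–3 | 6 | 12 | 6–13 | 6 / 1 |
| 4–6 | 13 | 19 | none (on a phase boundary) | not split |
| 7–9 | 19 | 25 | 19–36 | 6 / 11 |

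**Step 2: size by hand.** At sites 7–9 the control-coded months 19–25 centre on 22 and the intervention-coded months 25–36 on 30.5. The gap is 8.5 months, or 0.71 year. A trend of 1 point per year therefore puts 0.71 points into this contrast. The model averages it with properly adjusted contrasts, so the final bias is smaller.

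**Step 3: model.** Generalised least squares on half-month site cells, on the probability scale:

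- estimate = last element of (X′V⁻¹X)⁻¹X′V⁻¹y, where X holds the time levels and the coded indicator;
- V = σ²[(1 − ρ)/n on the diagonal + ρc for any two cells of a site + ρ(1 − c) for two cells of a site in the same period];
- ρ = 0.01 and c = 0 (Sample size); n = (40/6) × 0.5 = 3.33 per cell;
- σ² = (0.07 × 0.93 + 0.14 × 0.86)/2 = 0.0928, or pooled 0.105 × 0.895 = 0.0940;
- power = Φ(0.07/SE − 1.96), taking alpha as two-sided (the article does not say).

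**Step 4: the plan's own figure.** Four equal phases of 240/4 = 60 per site, without the offset, give 80.6% (or 80.1% pooled). The stated 80% is reproduced, but only with equal phases. The calendar in Step 1 (about 40, 47, 40 and 113 per site), without the offset, gives 71–72%.

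**Step 5: bias with a true effect of zero.** Trend sizes are assumptions, because the article gives none.

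| Linear trend (points/year) | Spurious effect (points) | Share of 7 points | Two-sided type I error |
|---|---|---|---|
| 0.5 | 0.18 | 3% | 5.1% |
| 1 | 0.36 | 5% | 5.3% |
| 2 | 0.72 | 10% | 6.1% |
| 3 | 1.08 | 15% | 7.5% |

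The coefficient of 0.36 ranges from 0.29 to 0.40 over intra-cluster correlations of 0–0.02 and autocorrelations of 0–0.8. If the last phase ended at month 31, 34, 37 or 43 it would be 0.22, 0.31, 0.39 or 0.55. A logistic check without random effects, with a trend of 0.2 per year on the logit scale, gives a spurious odds ratio of 1.06–1.08. The planned odds ratio is (0.14/0.86)/(0.07/0.93) = 2.16.

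**Step 6: locating the cause** (trend of 1 point per year, mean variance, autocorrelation 0).

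| Time cuts | Indicator switches | Bias (points) | SE (points) | Power for 7 points |
|---|---|---|---|---|
| 6/13/19 | 12/19/25 (as written) | 0.36 | 2.35 | 84.6% |
| 6/13/19 | 6/13/19 (no offset) | 0.00 | 2.76 | 71.7% |
| 6/13/19 plus 12 | 12/19/25 | 0.34 | 2.39 | 83% |
| 6/13/19 plus 25 | 12/19/25 | 0.04 | 2.63 | 76% |
| 6/12/13/19/25 | 12/19/25 | 0.00 | 2.69 | 73.8% |
| 12/19/25 | 12/19/25 | 0.00 | 2.76 | 71.7% |

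Pooled variance lowers each power by about half a point: 84.1% as written, 73.3% and 71.2% for the last two rows.

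**The case against.** Four points can be made for the plan.

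- **The calendar is inferred.** No sentence gives the phase boundaries. The start dates appear where staff surveys are timed, and Fig. 1 is not shown. Table 2 gives a post-intervention phase of 9–12 months, and the Stage 2 section starts it at months 19, 25 and 28. Sites would then end somewhere between 19 + 9 = 28 and 28 + 12 = 40, not uniformly at 36. This stands as a limit on the size, hence the range of 0.22 to 0.55. It does not remove the misalignment.
- **The phases may have been meant to move with the indicator.** If so, the bias is zero and the plan is sound. But the text applies the offset to the indicator alone, and a statistician following it literally would fit the misaligned model. Both the time term and the offset are specified here, so this is not a detail left to the analysis plan.
- **The effect is modest.** This stands. For trends up to 2 points per year the type I error stays near 6%.
- **Alignment costs precision.** This also stands and is counted under the fix.

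A reader might go further in three ways that the documents do not support. The long last phase is not itself the fault: without the offset the bias is exactly zero with the same phase. Nor is all change within phases credited to the intervention: the share is about 36% of one year's drift. Finally, a 3-point step exactly at month 25 would give 1.4 points (20% of the target), but that is the worst case on a 7% control rate. The same step gives zero bias at months 1–6 or 13–19 and at most 0.31 points at months 7–12.

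**Conclusion.** The concern holds for the offset analyses of 6-month abstinence, and only there. As the article is worded, the coded switches at months 12 and 25 fall inside phases. Nearly all the bias comes from sites 7–9 at month 25; the month-12 switch for sites 1–3 adds little.

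The size is about 0.36 points per 1 point per year of linear trend, and 0.18 to 0.72 points for trends of 0.5 to 2 points per year. The sign follows the trend, so a falling trend would hide benefit. These figures assume that month 0 is the start of recruitment, that phases change at the start dates, that recruitment is even and ends at month 36, and the article's intra-cluster correlation and autocorrelation. The trend itself is an assumption. Outcomes analysed without the offset are not biased by a common trend. The point should be corrected, but it would not overturn a 7-point effect under the trends considered.

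**What to change.** For the analyses of 6-month abstinence, define both the fixed time factor and the time-within-site random effect by calendar periods whose boundaries include every shifted switch date: months 12, 19 and 25. Cuts at 6/12/13/19/25, or phases shifted to 12/19/25, both remove the linear-trend bias. A single added cut at month 25 removes about 90% of it ((0.361 − 0.038)/0.361). If the phases were always meant to move with the indicator, one sentence saying so is enough. Outcomes without the offset should keep periods aligned to the unshifted dates 6, 13 and 19; imposing cuts only at 12/19/25 on them would create the same mismatch in reverse. The actual calendar dates of the periods should be stated.

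The change is to wording only and needs no new data. Its cost is precision: the standard error rises from about 2.4 to 2.7–2.8 points. Nominal power for 7 points falls from roughly 84% to 71–74% at the stated intra-cluster correlation of 0.01 and autocorrelation of 0. The higher figure rests partly on the unadjusted contrast. The stated 80% should be recomputed for the model and calendar actually used.
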